## 3. Discussion

This protocol provides a detailed description of a multisite feasibility study to evaluate a novel hybrid teaching kitchen intervention aimed at improving health behaviors and outcomes. By combining in-person and virtual instruction, providing grocery ingredients, and integrating hands-on culinary skill development, nutrition education, physical activity promotion, mindfulness activities, and behavior change strategies, this protocol, and the study it is connected to, sets the stage for future investigations of a range of teaching kitchen and other Food Is Medicine and Whole Person Health educational interventions. 

The importance of this study lies in its potential to inform the development and implementation of effective and scalable interventions to address the growing incidence of chronic disease. 

Limitations of this study include its duration, intensity, and eligibility criteria, which could make recruitment challenging. Adults who meet the BMI and lab value criteria but are not yet on medications are a smaller subset of the U.S. population to identify and recruit. The time commitment is anticipated to limit the number of people who will be interested in this study; while there has been thoughtful consideration around the time the classes are scheduled (after work evening hours), it is unlikely to be practical for some. Access to groceries may be challenging at individual study sites. This and the location of grocery pick-up may be a limiting factor for some potential participants. Participants must also have two Internet-capable devices and be capable of operating them independently. This may limit participation. Considerations and adaptations have been made to the curriculum itself to account for regional differences in foods and flavor profiles; however, the curriculum is only being offered in English, which limits implementation and evaluation of this protocol to English-speaking populations only. 

By evaluating the feasibility and acceptability of a hybrid teaching kitchen model, this study aims to inform strategies for implementing similar interventions across diverse populations while addressing barriers to participation. In addition, the assessment of lifestyle behavior changes and biometric data will offer valuable contributions to the burgeoning Food as Medicine movement and the field of integrative medicine, emphasizing the potential of culinary education to promote health and well-being. Additionally, this study supports the growing call to enhance nutrition education in medical schools and to reintroduce home economics in elementary schools as foundational tools for lifelong health literacy. Notably, this multisite teaching kitchen intervention is the first to operationalize the dual assessment of pathogenesis and salutogenesis, as articulated by Helene Langevin and the NIH, aligning with the framework presented in her 1 November 2024 NCCIH talk in Washington, DC.

This protocol description highlights the value of sharing a robust and potentially transformative multi-institutional effort to investigate teaching-kitchen-related curricula and other Whole Person Health and Lifestyle Medicine educational interventions. By detailing the study design, methodology, and planned assessments, this paper underscores the importance of creating a replicable framework for evaluating such interventions. This approach not only contributes to the growing evidence base for innovative health education strategies but also provides a foundation for future studies seeking to explore the effectiveness of integrative and lifestyle-focused models. Sharing this protocol supports transparency, fosters collaboration, and encourages adaptation of these interventions to diverse populations and settings, ultimately advancing the fields of health promotion and preventive care.

If successful, this intervention has the potential to produce significant public health impact by improving dietary habits, increasing physical activity, and enhancing overall health and well-being. By addressing multiple health behaviors simultaneously, this comprehensive approach may lead to greater and more sustained improvements in health outcomes compared to single-component interventions.

## Figures and Tables

**Figure 1 nutrients-17-00314-f001:**
[figure not shown]
Teaching Kitchen Multisite Trial (TK-MT) Study Flowchart.

**Table 1 nutrients-17-00314-t001:** Biometric Inclusion Values for Study Eligibility (must have at least one of the following abnormal values).

Biometric Marker	Minimum Level for Eligibility	Maximum Level for Eligibility
Fasting Glucose	100 mg/DL	125 mg/DL
Hemoglobin A1C	5.70%	6.40%
Triglycerides	150 mg/DL	No upper limit
HDL	No lower limit	Men: <40; Women: <50
LDL	100 mg/DL	No upper limit
ALT	Men: >55 unit/L; Women: >30 unit/L	No upper limit

Participants must have at least 1 eligible biometric marker in addition to 25 ≤ BMI < 40 to meet inclusion criteria for this study.

**Table 2 nutrients-17-00314-t002:** TK-MT Study Assessments.

Timepoint	Evaluation Measures	Intervention Group	Control Group
Baseline	Anthropometric measurements	At study site with RA	At study site with RA
	Biometric measurements	At designated lab facility	At designated lab facility
	Psychometric assessments	Email link to REDCap surveys	Email link to REDCap surveys
Core Phase (Class 1–16)	Weekly participant satisfaction	Email link to REDCap surveys	N/a
	Weekly participant photo upload	Email link to REDCap surveys	N/a
	Participant worksheet uploads	Email link to REDCap surveys	N/a
Week 16 (4-month assessment)	Anthropometric measurements	At study site with RA	At study site with RA
	Biometric measurements	At designated lab facility	At designated lab facility
	Psychometric assessments	Email link to REDCap surveys	Email link to REDCap surveys
Booster Phase (Class 17–24)	Monthly participant satisfaction	Email link to REDCap surveys	N/a
	Monthly participant photo upload	Email link to REDCap surveys	N/a
	Participant worksheet uploads	Email link to REDCap surveys	N/a
12-month assessment *	Anthropometric measurements	At study site with RA	At study site with RA
	Biometric measurements	At designated lab facility	At designated lab facility
	Psychometric assessments	Email link to REDCap surveys	Email link to REDCap surveys
	Program feedback surveys	Email link to REDCap surveys	N/a
	Interviews (participants)	Email login info for interview	N/a
18-month assessment	Anthropometric measurements	At study site with RA	At study site with RA
	Biometric measurements	At designated lab facility	At designated lab facility
	Psychometric assessments	Email link to REDCap surveys	Email link to REDCap surveys
	Program feedback	N/a	Email link to REDCap surveys

*. Program feedback survey will be completed by participants and research staff at the 12-month assessment point.

**Table 3 nutrients-17-00314-t003:** TK-MT Intervention Overview.

Class Type	Cooking and lifestyle instruction by chef educators, registered dietitians, and lifestyle experts. ○ In-person: classes 1 and 2. ○ Virtual: classes 3–24.		
Class Duration	12-month program. ○ 2 h/session. ▪ 16 weekly classes (core classes). ▪ 8 monthly classes (booster classes).		
Class Structure	Introduction and discussion of class objectives. Didactic education on selected nutrition and lifestyle components with group discussion or worksheet opportunities. Discussion of recipe and ingredients. Cooking of recipe. Mindful exercise, meditation, or physical activity. Taste and eat prepared meal and discuss shared experiences. Time for open discussion, reflection, and/or troubleshooting.		
Behavioral Framework	Observational/ hands-on learning. Social influence.	Self-efficacy. Knowledge building. Attitudes and beliefs.	Peer support. Skill development and practice.
Wellness Domains	Social. Emotional. Spiritual.	Intellectual. Physical. Environmental.	Financial. Occupational.

**Table 4 nutrients-17-00314-t004:** Primary Feasibility Outcomes of the Teaching Kitchen Multisite Trial.

Indicator	Quantitative Assessment	Qualitative Assessment
Recruitment Rate	$\left(\frac{\#randomized}{\#screened}\right)\times 100\%$ REDCap randomization module. REDCap screening survey (completion status).	Barriers and facilitators to recruitment based on: Notes from each site’s research team. Feedback from individuals who choose not to participate. Participant feedback during post-study interviews.
Retention rate	$\left(\frac{\#attended>80\%\;classes}{\#randomized}\right)\times 100\%$ REDCap class participation survey (attendance item). REDCap randomization module.	Barriers and facilitators to retention based on: Notes from each site’s research team. Feedback from participants who choose to withdraw from the study.
Attendance rate (per participant)	$\left(\frac{\#classes\;attended}{\#total\;classes}\right)\times 100\%$ REDCap class participation survey (attendance item).	Barriers and facilitators to attendance based on: Notes from each site’s research team. Self-reported free text response to why a class was missed in REDCap class participation survey. Feedback from participants during post-study interviews.
Participant engagement	Post-class recipe photo upload rate = $\;\;\frac{\Sigma \left(\frac{\#recipe\;photos\;uploaded}{\#total\;recipes}\right)}{\#intervention\;participants}\times 100\%$ Post-class worksheet upload rate = $\;\;\frac{\Sigma \left(\frac{\#worksheets\;\;uploaded}{\#total\;worksheets}\right)}{\#intervention\;participants}\times 100\%$	Barriers and facilitators to participant engagement based on: Notes from each site’s research team. Feedback from participants during post-study interview.
Intervention fidelity	Session fidelity = $\bar{fs_{i}}$ , where *fs_i_* = post-class fidelity checklist (possible score of 0–14 points).	Barriers and facilitators to intervention fidelity based on: Free text response to post-class fidelity checklist items. Feedback from staff in the end-of-study staff surveys.
Intervention resources	Planned intervention costs vs. actual, grocery, labor, and overhead costs.	
Average class satisfaction (cs) rate Average class recipe satisfaction (rs) rate	REDCap class satisfaction survey = $\frac{\Sigma \bar{cs_{i}}}{\#respondents}\times 100\%$ REDCap recipe satisfaction survey = $\frac{\Sigma \bar{rs_{i}}}{\#respondents}\times 100\%$	Barriers and facilitators to individual session acceptability based on: Notes from each site’s research team in the REDCap implementation form. Free text response to perception of the class, recipe, and grocery experience following each class session in the REDCap class participation survey. Feedback from participants during post-study interviews.
Overall program acceptability	Program satisfaction (5-pt Likert scale). Recipe ease (5-pt Likert scale). Recipe preparation success (5-pt Likert scale). Intent to continue using recipes (yes/no). Top 3 recipes. Perceived cultural appropriateness (yes/no). Most helpful program component. Skills learned. Food access. Cooking equipment access. Likelihood to recommend the program. Surprising and inspiring program components.	Barriers and facilitators to overall program acceptability based on: Free text responses to the end of intervention survey. Feedback from participants during post-study interviews.

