#### 2.3.2. Sample Size Estimation

A proposed sample size of 320 participants (4 study sites × 2 cohorts × 20 participants per arm) will have 80% power to detect significant improvements in metabolic syndrome biomarkers ranging from 14.2 to 30.15%, assuming that control group participants have improvements ranging from 5 to 15% for ɑ = 0.05 by using a two-sample *t* test. Power analysis calculations for sample size are based on reported effect size estimates of metabolic syndrome markers (Appendix A) [44].

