#### 2.3.3. Recruitment and Randomization

Potential participants will be recruited through the TK-MT website, paid social media advertisements, physical and digital flyers, social media postings, institutional emails, television spots, ads in community newspapers, booths at health fairs, and referrals from research or clinical staff at the study sites. Study recruitment will follow the process outlined in Figure 1. Preliminary study eligibility will be assessed through an optional pre-screening survey on the TK-MT website followed by a screening phone call.

Alternatively, interested individuals can call the study team directly and complete a phone call screening. Those who are likely eligible based on the phone call screening will complete a follow-up video call with a trained research assistant (RA). These screening methods will collect eligibility data and visually confirm minimal operating kitchen equipment described in the inclusion criteria. The RA will explain the study details and obtain informed consent during these screening calls. Final eligibility will be confirmed by study site PI based on a review of anthropometric data, laboratory data, self-reported medication lists, and study site MD recommendations.

Eligible participants will be randomized at the site level in blocks to either the TK-MT intervention group or the wait-list control group receiving standard care (i.e., followed as usual by their primary care physician). Each site will independently enroll 1–2 cohorts and randomize 28–48 participants to each study arm (for single-cohort sites) or 14–30 participants per arm (for double-cohort sites); the wait-list control group will receive a condensed version of the intervention curriculum after completing the 12-month assessments. Individuals who share a household can participate in this study only if they have separate kitchen workspaces for virtual classes and must be randomized to the same study arm. All recruitment and randomization data will be documented in site-specific REDCap surveys and forms. Incentives, in the form of gift cards and small gifts (notepad, measuring spoons, etc.) valued at a total of USD 200 per individual will be provided after completing (1) laboratory and anthropometric screening, (2) baseline psychometric assessments, (3) 4-month assessments, (4) 12-month assessments, and (5) 18-month assessments.

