### 2.4. Study Procedure

The intervention group will be provided with 16 weeks of intensive, hands-on culinary and lifestyle skills instruction (2 in-person and 14 virtual), followed by 6 monthly, virtual classes. Intervention and control group participants will be assessed at baseline, 4 months, 12 months, and 18 months. Control group participants will be provided with 2 in-person and 14 recorded videos of intervention classes after the 12-month assessment timepoint. See Table 2 for assessment timetable. Enrollment began in August 2023 and all participant study activities will end in October 2025.

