#### 2.4.1. TK-MT Intervention

The 12-month TK-MT intervention program will be delivered by a culinary educator, a registered dietitian, and behavioral/lifestyle experts with health coaching and motivational interview training. There will be a minimum of two instructors facilitating each class; facilitator roles may change throughout intervention. The first 2 in-person classes will be held at academic or community-based teaching kitchens affiliated with each study site. For subsequent classes, participants will join via a video conferencing platform and cook in their home kitchens while facilitators lead from a teaching kitchen. The first 16 core classes (classes 1–16) will be held weekly and last approximately 2 h. The remaining 8 booster classes (classes 17–24) will be held monthly and last approximately 2 h. RAs trained in intervention implementation will be present during classes to assist participants. An overview of the TK-MT educational intervention is detailed in Table 3.

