#### 2.5.1. Primary Outcomes

The primary aim of this study will be to assess the feasibility of implementing the TK-MT. Feasibility will be evaluated across common trial-level and intervention-level outcomes [48]. Trial-level feasibility outcomes are recruitment capacity and retention. Intervention-level feasibility outcomes are participant attendance, participant engagement, intervention fidelity, intervention resources, and participant and staff acceptability. The detailed data collection methods that will be used to measure feasibility outcomes are described in Table 4.

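### The primary outcome retention is defined in Table 4 as class adherence: controls cannot count as retained, the rate tops out at 50% if both arms are in the denominator, and no primary indicator gives follow-up completion

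*Protocol article*

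**What the plan says.** Section 2.5.1 splits the primary feasibility outcomes into two levels. At the upper level, "Trial-level feasibility outcomes are recruitment capacity and retention". Participant attendance is listed separately, at intervention level.

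Table 4 gives the retention rate as a fraction whose source reads "attended>80\%\;classes}{\#randomized", times 100%. The numerator comes from the attendance item of the class participation survey and the denominator from the randomisation module.

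Two other rows show how Table 4 uses its terms. The recruitment rate has the number randomised as its numerator, and its sources are "REDCap randomization module. REDCap screening survey (completion status"). The engagement rows, which concern one arm only, divide by a differently named count: "intervention\;participants}\times 100".

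Sections 2.4 and 2.4.2 give controls usual care for 12 months, then two in-person classes and recordings of classes 3 to 16. Section 2.4 and Table 2 schedule assessments for both arms at baseline, 4, 12 and 18 months. Section 2.7 says that reasons for non-completion will be recorded and that missing data from dropout will be examined in a sensitivity analysis.

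On the class total, section 2.4 has 16 weekly classes "followed by 6 monthly, virtual classes", while section 2.4.1 says "The remaining 8 booster classes", numbered 17 to 24.

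**The concern.** The label and the formula describe different things. Retention at trial level means staying under observation: the share of randomised people who are still assessed at follow-up. The printed formula counts people who came to most classes. Someone who attends 17 of 24 classes (70.8%) and completes every assessment is not retained. Someone who attends 20 of 24 (83.3%) and then misses the 12- and 18-month assessments is retained. A control who completes every visit is not retained.

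The introduction says that the findings are to inform a larger trial. Its planners need follow-up completion by arm, to inflate the sample size and to judge differential dropout in a wait-list design. The printed rate supplies neither, and a reader who takes it at face value would conclude that follow-up was poor.

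**Working it through.** **Inputs**
- Planned size, section 2.3.2: "320 participants (4 study sites × 2 cohorts × 20 participants per arm").
- Allocation, section 2.3.3: "randomize 28–48 participants to each study arm (for single-cohort sites) or 14–30 participants per arm (for double-cohort sites"). One range serves both arms.
- Offered to controls, sections 2.4 and 2.4.2: 2 in-person classes and 14 recordings, after month 12.
- Class total T: 16 + 6 = 22 (section 2.4), or 16 + 8 = 24 (section 2.4.1 and Table 3; the abstract and Table A2 also give 24).

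**1. The plan's own figure.** 4 sites × 2 cohorts × 20 per arm × 2 arms = 320, so 160 per arm. As a check on the equal split, a two-sided two-proportion test at alpha 0.05 with 160 per arm (pooled variance, no continuity correction) has power 0.801, 0.803 and 0.806 for 5% vs 14.2%, 10% vs 21.4% and 15% vs 27.9%. This matches the 0.5 rows of Table A1. The article states no retention value or target, so there is none to reproduce.

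**2. Can a control pass the cut?** Live classes only: 2/24 = 8.3%, or 2/22 = 9.1%. With every recording counted as attended: 16/24 = 66.7%, or 16/22 = 72.7%. Neither exceeds 80%.

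**3. Ceiling of the formula.** With no controls in the numerator, and a the share of the intervention arm above the cut:

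rate = a × 160 / 320 if both arms are in the denominator; rate = a × 160 / 160 if only the intervention arm is.

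| a | both arms | intervention arm only |
|---|---|---|
| 60% | 30% | 60% |
| 70% | 35% | 70% |
| 80% | 40% | 80% |
| 90% | 45% | 90% |
| 100% | 50% | 100% |

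Assessment completion does not enter either column. Each value is the same whether all 320 people or far fewer attend the 12-month visit.

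**4. Which denominator?** The recruitment rate uses the same count from the same module, and there it must cover both arms. Where Table 4 means one arm, it names that arm. The table's usage therefore points to both arms, but the article does not say so outright.

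**5. Where the cut falls.** The smallest whole number above 0.80 × T: for T = 22, 17.6 gives 18 classes (81.8%); for T = 24, 19.2 gives 20 classes (83.3%).

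**The case against.** The best defence is that the row was meant for the intervention arm. Its numerator comes from a class survey, and Table 2 marks the class-phase surveys as not applicable to controls, so an analyst might restrict the denominator without comment. That is a fair reading, and it removes the 50% ceiling. It does not make the measure retention, and it leaves the control arm with no retention figure among the primary outcomes.

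One could also score controls against their own abbreviated programme of 16 items, where 13 of 16 (81.3%) would pass. That requires viewing a recording to count as attending a class. The article does not say so, and the result would describe only the period after month 12.

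Several stronger readings are tempting, and the document does not support them:
- *Loss to follow-up goes unrecorded.* Section 2.7 records reasons for withdrawal or attrition and plans a dropout sensitivity analysis, and the retention row collects feedback from people who withdraw. What is absent is a completion rate among the primary indicators.
- *The trial would be declared a failure despite perfect follow-up.* No target or progression threshold is stated, and feasibility is summarised descriptively. The risk is misreading.
- *The row duplicates the attendance row.* They share a data item, but one is a percentage per participant and the other a proportion of people above a cut.
- *Differential dropout could never be known.* Visits are scheduled in both arms, so completion by arm can be derived. The printed indicator just does not report it.

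Finally, an article may leave detail to a fuller plan. That does not cover this point, because the article prints an explicit formula for a named primary outcome and the formula does not fit the name.

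**Conclusion.** The point holds in this form: Table 4's retention rate is class adherence, controls cannot enter its numerator, and no primary feasibility indicator quantifies completion of the follow-up assessments in either arm.

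The size depends on the denominator. With both arms, which Table 4's usage favours, the rate cannot exceed 50% at 1:1, and 70% adherence in the intervention arm would print as 35%. With the intervention arm only there is no ceiling, and the defect is the mislabelling and the missing control arm. The ceiling assumes equal allocation and attendance judged against the 22- or 24-class programme. It does not depend on reaching 320.

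No hypothesis test or sample size rests on this rate, but it is a primary outcome with a stated rule that gives a misleading number, so it should be corrected. The conflict over 22 or 24 classes is secondary: the lower total follows only from section 2.4, and it shifts the cut by two classes.

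**What to change.** In Table 4, define retention as the number completing the 12-month assessment divided by the number randomised, and likewise at 4 and 18 months, overall and by arm. State what counts as a completed assessment. Keep the present measure, but call it adherence (more than 80% of classes) and divide by the number randomised to the intervention. Carry both definitions into section 2.7.

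Reconcile the class total in section 2.4 with the abstract, section 2.4.1, Table 3 and Table A2, so that the attendance denominator and the 80% cut are fixed.

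The cost is wording. Assessments are already scheduled in both arms (Table 2) and randomisation is already recorded in REDCap (section 2.3.3), so no new data are needed.
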